### Feasibility and Sample Size

To test the primary hypothesis that a peer-mentored employment readiness intervention will have better self-determination (Arc’s self-determination) [59], career maturity inventory [60], and parental support (multi-dimensional scale of perceived social support) [61] compared to youth in a non-mentored group, it is expected that a *t* test will be used. Following the guidelines of Cohen [62] and Hertzog [63] we estimated that with an alpha of .05, power of 80%, and a medium effect size (ie, 0.50), a sample size of 80 (40 in each group; experimental and control) is needed [62]. This sample is suitable for a feasibility pilot [62-64]. Data collection will take 18 to 24 months (recruited in 10 by 8 groups), including control and experimental over 4 weeks.

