### Quantitative Data Analyses

Quantitative data will be analyzed using SPSS, version 22. Rates of accrual, dropout, and compliance (ie, attendance and number of postings) will be calculated. Descriptive statistics will be used to provide an overview of sample characteristics using means and standard deviations for continuous factors and frequencies and proportions for categorical factors. We will use an intent-to-treat approach to our analysis. It is expected that *t* test and chi-squared analyses will be conducted to test intervention effects (comparing baseline primary outcome measures (time 1) and post-test (time 2) data. Separate analyses will be conducted for each outcome. To control for type I error rate, Holm’s sequential correction will be applied. Effect sizes for *t* tests and Cohen *d* will be reported [62]. A *P* value of less than .05 will be used as the criterion for statistical significance.

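### Forty per group does not give 80% power for d = 0.50 at alpha .05: the stated t test has about 60% power two-sided (72% one-sided), before Holm, clustering and dropout.

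*Protocol article*

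**What the plan says.** Feasibility and Sample Size sets out the primary hypothesis that mentored youth will do better than non-mentored youth on self-determination, career maturity and perceived social support. It names a t test and an alpha of .05, and from these it states "power of 80%, and a medium effect size (ie, 0.50), a sample size of 80 (40 in each group; experimental and control) is needed". It then adds that this number suits a feasibility pilot, and says that recruitment will be in eight groups of ten.

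Quantitative Data Analyses plans a separate analysis for each outcome. For multiplicity it says that Holm's "sequential correction will be applied". The significance criterion is a P "value of less than .05 will be used as the criterion for statistical significance"; whether tests are one- or two-sided is not stated. On attrition it says "Rates of accrual, dropout, and compliance (ie, attendance and number of postings) will be calculated". The sample-size paragraph contains no allowance for dropout, for the Holm threshold or for shared forum groups.

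**The concern.** Alpha, power, effect size and test together fix the sample size. For a two-group t test at d = 0.50, 40 per group looks far too few for 80% power, and the gap is too large for rounding.

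The claim is attached to the primary efficacy hypothesis, so it shapes how the result will be read. A reader told that power is 80% takes the risk of missing a true d = 0.50 to be one in five. If that risk is really about two in five or more, a non-significant result says much less against e-mentoring than it would seem to. A later trial that reused the calculation would also be too small.

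**Working it through.** **Inputs from Feasibility and Sample Size:** alpha = .05; power = 80%; d = 0.50 (standardised, so SD = 1); 40 per group, equal allocation; t test between groups. Sidedness is not given, so both are shown.

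**1. Sample size for the stated inputs.** Normal approximation: n per group = 2(z_alpha + z_power)² / d².
- Two-sided: 2(1.960 + 0.842)² / 0.25 = 62.8, so 63. The noncentral t gives 63.8, so **64 per group, 128 in all**.
- One-sided: 2(1.645 + 0.842)² / 0.25 = 49.5, so 50. The noncentral t gives 50.2, so **51 per group, 102 in all**.

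The stated 80 is short by 128 − 80 = 48 (two-sided) or 102 − 80 = 22 (one-sided). It does not reproduce.

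**2. Power at 40 per group.** Noncentrality = d√(n/2) = 0.50 × √20 = 2.236.
- Two-sided: Φ(2.236 − 1.960) = 0.609 by the normal approximation; **0.598** by the noncentral t.
- One-sided: Φ(2.236 − 1.645) = 0.723 by the normal approximation; **0.716** by the noncentral t.
- Effect detectable with 80% power, two-sided: (1.960 + 0.842) / √20 = 0.63; the noncentral t gives **d = 0.634**.

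**3. Other readings of the figure.**
- Eighty per group instead of 80 in all: power 0.88.
- Paired (before-after) t test: 33.4, so 34 participants.
- Change-score t test at 40 per group: power 0.60 if the pre-post correlation is 0.5, and 0.81 if it is 0.7 (both assumed).
- ANCOVA at 40 per group: power 0.79 if that correlation is 0.6 (assumed).

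The article names a t test and gives no correlation, so none of these is the stated calculation.

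**4. Further losses.** Each is applied alone to 40 per group, d = 0.50, two-sided, noncentral t.

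| Source | Setting | Power |
|---|---|---|
| First Holm step, 2 outcomes | alpha .025 | 0.48 |
| First Holm step, 3 outcomes | alpha .0167 | 0.42 |
| Dropout 10% (assumed) | 36 per group | 0.55 |
| Dropout 15% (assumed) | 34 per group | 0.53 |
| Dropout 20% (assumed) | 32 per group | 0.50 |
| Forums of 10, ICC 0.01 (assumed) | 40/1.09 = 36.7 effective | 0.56 |
| Forums of 10, ICC 0.05 (assumed) | 40/1.45 = 27.6 effective | 0.45 |

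The design effect is 1 + (10 − 1) × ICC. The forum size of ten comes from the Intervention section. Two Holm rows are shown because Feasibility and Sample Size names three measures, while Quantitative Data Collection lists two as primary youth outcomes. One illustrative combination (three outcomes, ICC 0.02, 10% dropout) gives about 0.32.

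**The case against.** The core arithmetic is hard to dispute, but several points on the other side deserve weight.

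- **Sidedness.** The hypotheses are directional, so a one-sided test may have been meant. Power is then 0.72 and the miss rate about 28%, not 40%. This stands as a condition on the 60% figure; it does not restore 80%.
- **The Holm figure.** The 0.42 is power at the first step only, and Holm relaxes the threshold after each rejection. In simulation, with three outcomes all at d = 0.50, average power per outcome is about 0.49. The chance of at least one rejection runs from about 0.68 (assumed between-outcome correlation 0.5) to 0.81 (correlation 0: 1 − 0.579³ = 0.806). So 0.42 must be labelled as a first-step value, not as the power under Holm.
- **Unstated assumptions.** A strong pre-post correlation would bring power to about 80%. A paired test with 15% attrition would give 34/0.85 = 40. Neither assumption is in the article, and a paired test within one group would not test the between-group hypothesis. The finding is that the figure does not reproduce as stated; how it arose cannot be known.
- **Dropout and clustering.** The article gives no dropout rate and no ICC; it says only that dropout will be calculated. The direction of these losses is clear, but their size is assumed.
- **Pilot status.** The article already calls 80 suitable for a feasibility pilot and speaks of initial efficacy. That supports keeping 80. It does not correct the 80% power given for the primary hypothesis in the sentence before.

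**Conclusion.** The concern holds. For the test and inputs that the article states, 40 per group gives 60% power two-sided or 72% one-sided. Reaching 80% takes 64 or 51 per group. With 40 per group the two-sided test has 80% power only for d of about 0.63.

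These figures rest on a two-sample t test with equal variances, one outcome at .05, independent participants and complete data. Holm's correction, which is planned, lowers power per outcome to between 0.42 (first step, three outcomes) and about 0.49 (average when all three outcomes have d = 0.50). Dropout and forum clustering lower it further by an amount that depends on rates the article does not give. The stated power is wrong under either sidedness and should be corrected.

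**What to change.** Keep the sample of 80 and rewrite the sample-size paragraph, for example:

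> The sample of 80 youth (40 per arm) was chosen as a feasibility size. With a two-sided t test at .05 for one outcome, before Holm's correction, clustering by forum group and dropout, it gives about 60% power for d = 0.50 and 80% power for d = 0.63. At the first Holm step for three outcomes, power for d = 0.50 is about 42%. The efficacy comparison is preliminary.

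The rewrite should:
- drop the statement that 80 are needed for 80% power;
- state the sidedness and the number of outcomes in the Holm family (with two outcomes, the first-step figure is about 48%);
- say that the 80 are youth. If parents were counted within the 80, leaving 20 youth per arm, power would be 0.34. The wording of the hypothesis and the separate parent groups make that reading unlikely, but one word would rule it out.

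The cost is one reworded paragraph and a less favourable stated power. No participants are added, and the design and analysis do not change.

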### Procedures and Randomization

Ethical approvals will be obtained from a pediatric rehabilitation hospital and a University Research Ethics boards prior to starting. Informed consent will be acquired from all participants prior to taking part. Once participants have consented, a blocked randomization method will be used. Using a block size of 10, participants are randomly assigned to the appropriate treatment condition as they enroll in the study until the block is completed. Then the following 10 participants are assigned to the next block [65,66]. Participants are blinded to each other, unaware of any manipulation. To avoid contamination, we asked participants not to share their password.

### Quantitative Data Collection

After randomization, a member of the research team asks each participant (parents and youth) to complete an online survey (pre-test) via Fluid Surveys (approximately 30 minutes to complete), stored on a secure site at a pediatric rehabilitation hospital. When complete, they are given password-protected access to the intervention through AbilityOnline. Following the intervention, participants complete a post-test survey containing the measures listed below. Demographic measures include: age, gender, type of disability, any assistive devices, education level, and access. Use and comfort level with computers and the Internet is collected at baseline to describe control and experimental groups and to assess whether they have similar characteristics.

Primary youth outcome measures include the following standardized measures, all of which have good internal consistency, construct related and criterion validity, test-retest reliability, and have been widely used for youth with disabilities [59-61]: (1) Career Maturity Inventory-Attitude Scale [60,67], a 25-item agree-disagree scale where responses form the basis for 5 subscales relating to career decision-making, including orientation, involvement, independence, compromise, and decisiveness; and (2) Arc’s Self-Determination Scale, a self-report measure that assesses self-determination for adolescents with disabilities [59] with subscales on autonomy, acting on the basis of preferences and abilities (post-school directions), goal setting, and task performance.

Measures used for both parents and youth include (1) the Multi-dimensional Scale of Perceived Social Support, a self-report measure assessing sources of social support [61]; (2) Family Empowerment Scale, a 34-item rating scale to measure empowerment in families with children who have a disability [68,69]; and (3) the Ragins and McFarlin Mentor Role Instrument [70,71] that assesses perceptions of mentoring relationships based on 5 mentoring roles in the career-related dimension and 6 mentoring roles in the psychosocial dimension and was developed based on Kram’s theory [51] of mentor roles. Secondary measures include online usage such as number of modules completed and usage patterns (ie, number of times logged in, length of time spent online, number and content of postings). These analytics will be built into the web-hosting Drupal platform [72].

## Results

Data collection for this study is in progress. The proposed analysis is outlined in further detail below.

### Quantitative Data Analyses

Quantitative data will be analyzed using SPSS, version 22. Rates of accrual, dropout, and compliance (ie, attendance and number of postings) will be calculated. Descriptive statistics will be used to provide an overview of sample characteristics using means and standard deviations for continuous factors and frequencies and proportions for categorical factors. We will use an intent-to-treat approach to our analysis. It is expected that *t* test and chi-squared analyses will be conducted to test intervention effects (comparing baseline primary outcome measures (time 1) and post-test (time 2) data. Separate analyses will be conducted for each outcome. To control for type I error rate, Holm’s sequential correction will be applied. Effect sizes for *t* tests and Cohen *d* will be reported [62]. A *P* value of less than .05 will be used as the criterion for statistical significance.

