**Results:**

Data collection is in progress. Planned analyses include pre-post measures to determine the impact of the intervention on self-determination, career maturity, and social support. A qualitative thematic analysis of the discussion forums will complement the surveys to better understand why certain outcomes may have occurred.

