### Design

Our design involves a feasibility RCT, embedded qualitative design [52] to assess the feasibility and initial efficacy of the e-mentoring employment readiness intervention. Mixed-method designs are commonly used when qualitative methods are embedded within a RCT [52]. This mixed-method, prospective, intention-to-treat RCT study involves an intervention group that receives the employment readiness modules and a peer e-mentor and a control group that receives the employment readiness modules only but can interact with others in their group (no e-mentor). Pre- and post-surveys (immediately following the completion of the intervention) will be conducted with both groups (ie, intervention and control). The qualitative component of the study involves analyzing the content of the discussion forums (described below).

The gold standard Medical Research Council Framework for the development and evaluation of RCTs guided our design [53]. We focus on the development and feasibility phases (to establish theoretical underpinnings and modeling to test the feasibility of key intervention components) [53]. The rationale, design, content, and length of our intervention is based on the following systematic reviews conducted by our team: (1) employment readiness interventions for youth with physical disabilities [20]; and (2) best practices of peer mentorship for improving school and work outcomes for disabled youth [54]. In addition, we conducted the following scoping reviews: (1) improving the inclusion of people with disabilities in the workforce [55]; and (2) mentoring practices for a diverse workforce [56]. Needs assessments of youth with disabilities and their parents regarding informational support for employment were also conducted [17,21].

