### Control Groups

The control groups (for both parents and youth) have access to the modules only and do not receive peer mentorship. A researcher posts the discussion topic for the week but does not reply or encourage any follow-up discussion. Youth and parent participants are able to discuss topics and interact with others in their group but it is not facilitated by a mentor.

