### Combining Data

A mixed-method, embedded qualitative RCT design [52] will help us understand any discrepancies between expected and observed outcomes, provide insight into participant experiences and reasons for their preferences, explain how e-mentors influenced employment readiness skills (for youth) and empowerment (for parents), and what types of social support were provided. Our objectives combine quantitative and qualitative data and we will follow the guidelines of embedded qualitative RCT analysis [52,73-75]. Our findings will inform the feasibility and initial efficacy of an e-mentor employment readiness intervention for youth with physical disabilities. We hypothesize that participants in the intervention group will have significantly higher career maturity scores, self-determination, perceived social support, and family empowerment compared to controls.

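### The analysis section describes the test of intervention effects as time 1 against time 2 and names no between-arm contrast, in conflict with the mentored versus non-mentored hypothesis

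*Protocol article*

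**What the plan says.** The Quantitative Data Analyses section is the only place that sets out the quantitative tests. It opens with "It is expected that *t* test and chi-squared analyses will be conducted" and gives their purpose as "to test intervention effects (comparing baseline primary outcome measures (time 1) and post-test (time 2) data". The parenthesis names two time points and no arm. The section adds an intention-to-treat approach, separate analyses per outcome, Holm's correction and a 0.05 criterion.

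The Results paragraph of the abstract uses the same framing: "Planned analyses include pre-post measures to determine the impact of the intervention on self-determination, career maturity, and social support".

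Elsewhere the question is between arms. Feasibility and Sample Size states the primary hypothesis as better scores "compared to youth in a non-mentored group, it is expected that a *t* test will be used", and sizes the trial at 40 per arm. Combining Data expects the intervention group to have "significantly higher career maturity scores, self-determination, perceived social support, and family empowerment compared to controls". The abstract's Objective and the Methods Objectives also set the intervention against controls.

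The control is active. Under Control Groups, controls "have access to the modules only and do not receive peer mentorship"; they may still talk to one another in their own forum.

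**The concern.** A change from time 1 to time 2 measures everything that happens in those four weeks: the modules, contact with other participants, familiarity with the questionnaire and, in one arm only, the mentor. The trial was randomized to isolate the last of these, and only a contrast between arms does so. Since both arms work through the same kind of employment content, improvement in both is plausible even if mentors add nothing.

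An analyst who follows the analysis section literally could run a paired test in the mentored arm and report a significant gain as an intervention effect. Another could run paired tests in both arms and infer an effect from significance in one and not the other. Neither tests the stated hypothesis. Holm's correction does not help, because it controls error across outcomes and does not alter which contrast is tested.

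**Working it through.** **1. The passages side by side.** The hypothesis, objectives and sample size refer to mentored against non-mentored. The analysis section and the abstract's Results paragraph refer to baseline against post-test. No sentence joins the two, for example by specifying a between-arm comparison of change.

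**2. The plan's own figure.** The stated total is 80 (40 per arm) for alpha 0.05, 80% power and effect size 0.50. A two-sided two-sample t test with those inputs needs 64 per arm, and 40 per arm gives power 0.60. One-sided, it needs 51 per arm, and 40 gives 0.72. A paired test on a standardised change of 0.50 needs 34 people. None of these gives 80, so the sample size does not settle which test was meant. That mismatch is a separate matter, and this point does not depend on it.

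**3. If a within-arm pre-post test were used.** Inputs: 40 per arm (document); two-sided 0.05 (level from the document, sidedness assumed); no mentor effect; shared gain g in SD units and pre-post correlation r (both assumed, as the document gives neither).

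The standardised change is dz = g / √(2(1 − r)), and the paired t test has noncentrality dz × √40. At r = 0.5, √(2 × 0.5) = 1, so dz = g. For g = 0.3 the noncentrality is 0.3 × 6.325 = 1.90; for g = 0.4 it is 2.53.

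| r | shared gain | mentored arm significant at 0.05 | at 0.05/3 |
|---|---|---|---|
| 0.5 | 0.3 SD | 0.457 | 0.286 |
| 0.5 | 0.4 SD | 0.694 | 0.517 |
| 0.7 | 0.3 SD | 0.666 | 0.486 |
| 0.7 | 0.4 SD | 0.890 | 0.774 |

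The last column is Holm's strictest step if the family is the three outcomes in the primary hypothesis, which is an assumption.

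The chance of significance in the mentored arm but not in the control arm is p(1 − p). At r = 0.5 this is 0.457 × 0.543 = 0.248 and 0.694 × 0.306 = 0.212. At 0.05/3 it is 0.204 and 0.250.

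A simulation of 4,000 trials with g = 0.3 and r = 0.5 gave 45% and 24% at the 0.05 level. The between-arm t test on the same data was significant in 4.7%.

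**4. If a between-arm test was intended.** Power for d = 0.50, 40 per arm, two-sided 0.05, participants treated as independent. The effective standardised difference is 0.50 for post-test only, 0.50 / √(2(1 − r)) for change scores, and 0.50 / √(1 − r²) with baseline adjustment. At r = 0.5 the last is 0.50 / 0.866 = 0.577.

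| assumed r | post-test only | change score | baseline-adjusted |
|---|---|---|---|
| 0.5 | 0.60 | 0.60 | 0.72 |
| 0.6 | 0.60 | 0.69 | 0.79 |
| 0.7 | 0.60 | 0.81 | 0.87 |

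**5. Limit of these figures.** They do not carry over to a model with forum as a random effect. The article implies eight groups of 10, which leaves 8 − 2 = 6 degrees of freedom for the arm comparison. Even with zero intraclass correlation, baseline-adjusted power on 6 degrees of freedom is about 0.58, 0.65 and 0.74 at the three values of r.

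**The case against.** The strongest reply is that a between-arm test is what the investigators mean. Feasibility and Sample Size expects a t test against the non-mentored group, the trial is sized as two arms, and the analysis section promises intention-to-treat, which matters mainly for a comparison of randomized groups. The parenthesis, which is never closed, could be naming the data that enter the test and not the contrast. This has real weight. A reader might infer that the trial will not test mentored against non-mentored at all; the article does not support that.

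It is also fair that the error rates in step 3 apply only under the within-arm reading, depend on an assumed gain and correlation, and fall for a single outcome once Holm's threshold is applied.

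A between-arm t test on post-test or change scores is valid in a randomized trial, so baseline adjustment is a gain in efficiency and not a condition of validity. The article does not say that chi-squared will be applied to the scale scores, so that is a secondary matter of clarity.

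What remains is that the one section fixing the analysis describes a different comparison from the hypothesis, and the abstract repeats it. This is stated text, so it is not a detail that a condensed article has merely left to a fuller plan. Pilot status softens the consequence but does not remove it: initial efficacy is among the primary objectives and a significance criterion is set.

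**Conclusion.** The point holds as a conflict to be reconciled. The analysis section and the abstract's Results paragraph describe a time 1 to time 2 comparison with no arm named, while the hypothesis, objectives and sample-size section call for mentored against non-mentored.

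Under the literal within-arm reading, with no mentor effect, a shared gain of 0.3 to 0.4 SD and r = 0.5, the chance of a significant result in the mentored arm is about 46% to 69% per outcome before Holm, and about 29% to 52% at 0.05/3. These rates are conditional on that reading and are not a forecast of the trial's error rate.

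Under the between-arm reading the type I error is sound, and the only loss is power: 0.60 for post-test only, or 0.60 to 0.81 for change scores, against 0.72 to 0.87 with baseline adjustment, for r from 0.5 to 0.7 and clustering ignored. The repair is the same on either reading.

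**What to change.** Reword the Quantitative Data Analyses section along these lines: *The intervention effect for each outcome is the difference between the mentored and non-mentored arms in post-test score, adjusted for the pre-test score (ANCOVA), reported as an adjusted mean difference with 95% CI. Within-arm changes from pre-test to post-test are descriptive only.* Bring the abstract's Results paragraph into line, and have Feasibility and Sample Size name the same analysis.

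State which variables, if any, the chi-squared tests are for. Deal with clustering within discussion groups separately, and do not quote the power figures above for a model with a forum effect.

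The cost is wording only. Both arms complete the pre-test before they are given access to the intervention, so the covariate is already collected and no visit, measure or participant is added. The change should be made and dated before outcome data are compared by arm.
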